**4-7-1** **Prohibited concomitant medications and therapies**

Treatment of shoulder stiffness and self-care are prohibited from 3 days before the procedure until the procedure. The application of compresses or ointments to the treated area is prohibited from the end of the post-treatment period until the end of the post-treatment observation, as it will affect skin observation.

**4-7-2** **Concomitant Restricted Drugs and Concomitant Restricted Therapies**

Not set.

**4-8.** **Cease Regulations**

**4-8-1** **Criteria for Discontinuation of Individual Research Subjects**

1. When the research subject requests discontinuation
2. If the subject is found to be ineligible for the study
3. When it is found that the subject does not meet the selection criteria or violates the exclusion criteria after consent is obtained
4. If the patient has been treated for shoulder stiffness and self-care from 3 days before the treatment until the treatment
5. When it is determined that the continuation of the study is difficult due to the occurrence of adverse events
6. Other cases in which the principal investigator determines that the research should be terminated.

**4-8-2** **Rules for Discontinuation of the Entire Study**

The principal investigator will consider discontinuation of this research in the event of an unexpected serious adverse event arising from this research. If the decision to discontinue this research is made by the Principal Investigator, the Principal Investigator will promptly inform the research subjects' physicians and other relevant personnel and will conduct examinations and take appropriate measures to ensure the safety of the research subjects. The principal investigator will also notify the Clinical research review board in writing within 10 days.

**4-9.** **Procedures for Administration of Research Medical Devices.**

The research device used for the research will be loaned free of charge by Saciperere Japan. Appropriate storage and management of the research equipment will be conducted following the instruction manual provided by the loaner (High Luminance LED Onkyu Device, January 2020, TAK SYSTEM INITIATIVE CORPORATION.

**4-10.** **Randomization Method**

As stated in 4-4-2. Randomization Blinding Methods

**4-11.** **Identification of source documents**

Source documents are data and other records obtained through a clinical trial. Electronic data such as case report forms, questionnaires, and acquired images are considered source documents.

**5. Criteria for Selection and Exclusion of Subjects for Clinical trial and Discontinuation of Clinical trial**

5-1. Inclusion Criteria

As stated in 4-3-1. Inclusion criteria

**5-2. Exclusion Criteria**

As stated in 4-3-2. Exclusion criteria

**5-3.** **Criteria for discontinuation of clinical trial**

Stated in 4-8. Cease Regulations

**6.** **Matters relating to the treatment of subjects of clinical trial**

Stated in 4-2. Types of clinical trials, methods, and procedures

**7.** **Evaluation of Efficacy**

**7-1. Efficacy Endpoints**

Primary endpoint: subjective symptoms (VAS)

Secondary endpoints: changes in skin temperature, baroreflex sensitivity (BRS), autonomic nervous system function (heart rate variability)

Exploratory endpoints: muscle properties observed by ultrasonography (luminance, muscle contraction, muscle thickness, etc.), changes in surface electromyography (amplitude, frequency, etc.)

**7-2.** **Evaluation, Recording, and Analysis Methods**

Stated in 9-1. Statistical Analysis Methods

**8. Evaluation of Safety**

**8-1.** **Safety endpoints**

Adverse event (skin burn)

Failure of the treatment device

**8-2.** **Evaluation, recording, and analysis methods**

**8-2-1 Adverse event**

Adverse event means any undesirable or unintended illness or disability, or any manifestation thereof, occurring to Research Subjects or others who used or were used to use the Research Equipment. (A causal relationship to the Research Equipment is not required. (However, for those occurring in persons other than the Research Subjects, it shall be limited to those suspected to be the result of the use of the Research Equipment.)

When an adverse event or a malfunction of the treatment device is observed, the principal investigator (or a sub-investigator) shall immediately observe the patient's general condition appropriately, take appropriate measures, and promptly document the incident in the case report form. The frequency of adverse events and failures will be analyzed at the end of the study.

However, in this study, skin abnormalities at the irradiation site will be addressed, but not limited to, if deemed necessary by the principal investigator.

Among adverse events, events for which a causal relationship with this study cannot be denied shall be treated as "disease, etc.".

**8-2-2 Failure of the treatment device**

A malfunction is defined as a failure in the quality, safety, or performance of research equipment, such as breakage or malfunction, regardless of whether the failure is due to the design, delivery, storage, or use of the equipment.

When an adverse event or failure of the treatment device is observed, the principal investigator (or sub-investigator) should immediately observe the patient's general condition, take appropriate measures, and promptly document the incident in the case report form. At the end of the study, the frequency of adverse events and failures of treatment devices will be analyzed.

**8-3.** **Methods for collecting, recording, and reporting information on diseases and failure of the treatment device**

Procedures for collecting, recording, and reporting information on diseases and failures of treatment devices shall follow the "Standard Operating Procedures for Responding to Disease Outbreaks".

**8-4.** **Response after the occurrence of disease, etc. or malfunction**

Follow the " Standard Operating Procedures for Responding to Disease Outbreaks.

**9.** **Statistical analysis**

**9-1.** **Statistical Analysis Method**

9-1-1 Background characteristics of the population

The background factors of the study population should be described with descriptive statistics (mean, standard deviation, median, quartiles, percentage (%), etc.).

**9-1-2 Analysis of the primary endpoint**

Subjective symptoms (VAS) measured over time before, immediately after, and 15 minutes after the procedure at the treatment site will be analyzed using one-way repeated measure ANOVA or Friedman's test.

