**4.** **Matters related to the content of the clinical trial**

**4-1.** **Primary and secondary endpoints**

**4-1-1.** **Primary endpoints**

Subjective symptoms (VAS)

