**9-3.** **Establishment of the number of cases**

This was a feasibility study, and the number of patients was not set on a statistical basis. The minimum number of patients who could feasibly be evaluated for the endpoints was approximately 5-7, and 10 patients were chosen to account for dropouts.

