**9-4.** **Significance Levels**

The significance level is p<0.05 for all tests.

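### An openly unsized feasibility study fixes its primary VAS analysis only as an overall test over three times at 0.05, which by itself gives no direction, no contrast with baseline and no size of change

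*Protocol*

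**What the plan says.** - **Aim.** Protocol section 3 sets out to verify whether a single treatment changes subjective symptoms on the VAS, among other measures, compared with before treatment.
- **Endpoint.** Section 4-1-1 gives it as "Subjective symptoms (VAS") and names no time point or change score. The observation list in section 4-6-2 collects two symptom scores on a VAS at each of the three times: pain from stiff shoulders, and stiffness.
- **Primary analysis.** Section 9-1-2 takes "Subjective symptoms (VAS) measured over time before, immediately after, and 15 minutes after the procedure" and says that they "will be analyzed using one-way repeated measure ANOVA or Friedman's test". It ties the readings to the treated area: "15 minutes after the procedure at the treatment site will be analyzed using one-way repeated measure ANOVA".
- **Level.** Section 9-4: "The significance level is p<0.05 for all tests".
- **Size.** Section 9-3: "This was a feasibility study, and the number of patients was not set on a statistical basis". It continues: "The minimum number of patients who could feasibly be evaluated for the endpoints was approximately 5-7", and "10 patients were chosen to account for dropouts".
- **Descriptive output.** Section 9-1-1 lists means, SDs, medians and quartiles for background factors. Section 9-1-2 lists none for the VAS.

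**The concern.** The stated rationale and the stated analysis do not fit together. A feasibility study whose size has no statistical basis is best placed to hand on an estimate: how far the VAS moved, how uncertain that is, and how variable the change was between people. The protocol instead fixes the primary analysis as a single test.

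An overall repeated-measures ANOVA or Friedman test asks only whether the three times differ somewhere. A small p-value does not say whether VAS fell or rose, which time differs from baseline, or by how much, so on its own it does not answer section 3. A large p-value from 5 to 10 people excludes very little, yet beside a yes/no aim and a 0.05 threshold it is easily taken as no change. At stake is the usefulness of the result to whoever plans the next trial of the device.

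**Working it through.** **Inputs from the protocol:** 10 enrolled and about 5-7 evaluable (9-3); three times and an overall test (9-1-2); alpha 0.05 (9-4). The protocol gives no effect size, SD or correlation between times, so those below are assumptions.

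**The plan's own figure.** There is no statistical derivation of 10 to reproduce. It would follow from 7/(1 − 0.30) = 10 or 5/(1 − 0.50) = 10, but no dropout rate is stated.

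**ANOVA power.** Assume normal data with SD σ and equal correlation ρ between times. The F test has 2 and 2(n − 1) degrees of freedom and noncentrality

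λ = n Σ(μ_j − μ̄)² / [σ²(1 − ρ)].

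The SD of a paired difference is σ_d, with σ_d² = 2σ²(1 − ρ), so λ = 2n Σ(μ_j − μ̄)² / σ_d².

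*Case A: change δ = 0.5 σ_d.*
- Sustained at both later times (means 0, δ, δ): Σ(μ_j − μ̄)² = (2/3)δ², so λ = 2n × (2/3) × 0.25 = n/3.
- Gradual (means 0, δ/2, δ): Σ(μ_j − μ̄)² = δ²/2, so λ = n/4.

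Friedman power for the sustained change was simulated with 20,000 runs per setting, using the chi-square critical value.

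| n | λ sustained | ANOVA, sustained | ANOVA, gradual | Friedman, sustained |
|---|---|---|---|---|
| 10 | 3.33 | 30% | 24% | about 22% |
| 7 | 2.33 | 21% | 17% | about 17% |
| 5 | 1.67 | 15% | 12% | about 11% |

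*Case B: sustained change of 0.5 σ, that is, 0.5 SD of the VAS itself.* Here λ = n/[6(1 − ρ)].

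| ρ | λ at n=10 | ANOVA power, n=10 | ANOVA power, n=7 |
|---|---|---|---|
| 0.3 | 2.38 | 23% | 16% |
| 0.5 | 3.33 | 30% | 21% |
| 0.7 | 5.56 | 48% | 32% |
| 0.8 | 8.33 | 66% | 46% |
| 0.9 | 16.67 | 93% | 77% |

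**Change detectable with 80% power by the ANOVA**, in SD of the paired difference (sustained to gradual pattern): 0.93-1.07 at n=10, 1.16-1.34 at n=7, 1.47-1.69 at n=5.

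**What an estimate would show.** The half-width of a 95% confidence interval for a mean change is t(0.975, n − 1)/√n, in SD of the change:
- n=10: 2.262/√10 = 0.72
- n=7: 2.447/√7 = 0.92
- n=5: 2.776/√5 = 1.24

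**The case against.** Much of the case on the other side stands.

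- **The small size is declared.** A feasibility study needs no power calculation, and where no power is claimed, low power is not an error.
- **A reader might infer that the trial will report no change whenever p exceeds 0.05.** No section says so. Section 9-4 sets a level, and the protocol has no success criterion or decision rule. This is a risk of misreading, not a planned rule.
- **A reader might infer that no effect estimate will be produced.** The document does not support that. Section 9-7 mentions an original statistical analysis plan, which is not shown, and means, SDs and intervals are commonly specified there. What can be said is that section 9-1-2 names none and defines the primary analysis as the overall test.
- **A reader might infer that a moderate change would usually be missed.** That holds for 0.5 SD of the paired difference. For 0.5 SD of the VAS itself it fails at n=10 once the correlation reaches about 0.8.
- **The overall test is not the only efficacy analysis in the trial.** Section 9-1-3 also plans before-to-after comparisons of heart rate variability and baroreflex sensitivity, and section 9-1-4 plans comparisons of electromyography and ultrasound. The point concerns the primary VAS analysis.

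None of this removes the mismatch. Added summaries in a separate plan would still leave the protocol's primary analysis as a test with no direction, contrast or size, for a question about change from baseline.

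**Conclusion.** The point holds as a mismatch between purpose, size and primary analysis, and it should be corrected. The mismatch can be read directly from sections 3, 9-1-2, 9-3 and 9-4 and needs no assumption.

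How often a real change would give p>0.05 does rest on assumptions: normal data, equal correlation between times, and an effect and variability that the protocol does not give. In case A the test misses the change in about 70-89% of trials, over 5 to 10 evaluable subjects, both patterns and both tests. In case B at n=10 the miss rate runs from 77% down to 7%. A non-significant result would therefore be hard to interpret, but no single miss rate can be attached to this trial.

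**What to change.** In section 9-1-2, define the primary result as the mean within-subject change from before treatment to each post-treatment time, for each of the pain and stiffness VAS scores, with its SD and 95% confidence interval. The investigators should name in advance which score and which time is primary; the protocol gives no ground for choosing these for them. Report the ANOVA or Friedman p-value as supportive, and state that p>0.05 is not evidence of no change. Use the same form for the continuous secondary endpoints in section 9-1-3.

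The cost is a few sentences, and the readings are already scheduled. The result will look less decisive. Precision does not improve: the interval shows how little 5 to 10 subjects can establish, and the SD of the change becomes available for planning the next trial.

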**9-1-3** **Analysis of secondary endpoints**

- On the treated side, the pre-, immediate post-, and 15-minute post-treatment tenderness meter and skin temperature measurements over time will be analyzed using one-way repeated measure ANOVA or Friedman's test.
- ~~One-way repeated measure ANOVA or Friedman's test will be used to analyze the pressure pain threshold, skin temperature, and subjective symptoms (VAS) measurements over time before, immediately after, and 15 minutes after the treatment on the non-treatment side.~~
- ~~Differences between the treated and non-treated sides of the pressure pain threshold, skin temperature readings, and subjective symptoms (VAS) over time before, immediately after, and 15 minutes after the treatment will be analyzed using two-way repeated measure ANOVA or Friedman's test.~~
- Heart rate variability frequency analysis will be performed to compare changes in the low frequency (LF) range and the power ratio of the low-frequency range to the high-frequency range (LF/HF) from before to 15 minutes after treatment. Average values will be taken before (5 minutes), ~~during (up to 3 minutes)~~, immediately after (5 minutes), and 15 minutes after (5 minutes) the procedure and analyzed using One-way repeated measures ANOVA or Friedman's test.
- Comparison of baroreceptor reflex sensitivity before, immediately after, and 15 minutes after the procedure

**Description maintenance (description error)9-1-4** **Exploratory analysis**

- Compare the changes (amplitude, frequency) in surface electromyography due to weight loading before and after 15 minutes of treatment
- Muscle properties (luminance, muscle contraction, muscle thickness, etc.) observed by muscle ultrasonography will be compared before and 15 minutes after the treatment.
- ~~Comparison of baroreceptor reflex sensitivity before, immediately after, and 15 minutes after the procedure~~

**9-2.** **Interim Analysis**

Not performed

**9-3.** **Establishment of the number of cases**

This was a feasibility study, and the number of patients was not set on a statistical basis. The minimum number of patients who could feasibly be evaluated for the endpoints was approximately 5-7, and 10 patients were chosen to account for dropouts.

**9-4.** **Significance Levels**

The significance level is p<0.05 for all tests.

**9-5.** **Discontinuation Criteria**

As stated in 4.8 cease Regulations

**9-6.** **Data Handling**

(Analysis Population)

Efficacy analyses will be performed on the largest analysis population (FAS). If necessary, a sensitivity analysis of efficacy will be conducted on a population that conforms to the research protocol (PPS).

(Safety analysis)

All study subjects (SP) will be included in the study, and subjects will be grouped according to whether or not they received the intervention. Consideration of the treatment of individual study subjects and determination of the attributable analysis population will be made before data fixation.

Reasons for Exclusion FAS PPS SP

|  | FAS | PPS | SP |
| --- | --- | --- | --- |
| Study subjects who did not receive any treatment | Exclusion | Exclusion | Exclusion |
| Study subjects who did not receive any investigation of efficacy endpoints | Exclusion | Exclusion | Included |
| Research subjects who violated the selection and exclusion criteria | Included | Exclusion | Included |
| Research subjects who deviated from the research protocol | Included | Exclusion | Included |

**9-7.** **Procedure for changing the analysis method**

The principal investigator shall revise the research protocol and explain any changes from the original statistical analysis plan in the clinical trial summary report.

**9-8.** **Selection of Analysis Subjects**

As stated in Data Handling

**10.** **Access to source documents, etc. (including the contents of contracts entered into under Article 32 of the Clinical Trials Act).**

The head of the institution and the principal investigator will provide direct access to all clinical trial-related records, including original documents, during monitoring, audits, and investigations by the Clinical research review board and regulatory authorities related to the research in question.

**11.** **Quality Control and Quality Assurance**

The Principal Investigator shall control and assure the quality of the clinical trial by having the monitors monitor the progress of this clinical trial to confirm that this clinical trial is being conducted appropriately following the research protocol and the Clinical trials Act. The principal investigator will prepare a separate monitoring protocol describing the items to be checked and the responsibilities of the parties involved, etc., and the monitors will conduct monitoring following the monitoring protocol.

No audits will be conducted.

**12.** **Ethical Considerations**

**12-1．Approval by a certified research review board**

The appropriateness of conducting this research will be reviewed and approved by the clinical research review board of the Hamamatsu University School of Medicine and approved by the administrator of the implementing medical institution.

**12-2.** **Benefits accruing to subjects of clinical trial**

Participation in this study is expected to provide relief from shoulder stiffness in the treated area. In addition, information derived from blood perfusion, contractile and relaxing functions in the shoulder muscles will be obtained and may be useful for future improvement of shoulder stiffness.

**12-3.** **Burden and foreseeable disadvantages to subjects of clinical trial**

Each study will require approximately one hour for preparation, treatment, and measurement.

The anticipated adverse event for the LED light acupuncture device is considered to be a burn of the skin at the treatment site.

**13.** **The handling and preservation of records (including data).**

**13-1.** **Provision of records to third parties**

Records (including data) obtained in this study will be anonymized at the implementing medical institution so that they cannot be identified at first glance, and will be sent to the following. When the information is provided, it will be managed responsibly by the principal investigator, and no correspondence will be provided to identify the information and individual research subjects. The information provided will be appropriately stored by the person in charge of the relevant medical institution as described below.

The information to be transferred, the name of the research institution, and the responsible person are as follows.

- Samples and records (including data) to be transferred

Records (including data): Records (including data) obtained in this study (excluding correspondence table)

- Name and responsible person of the research institute to which the transfer is to be made
  - The Graduate School for the Creation of New Photonics Industries; [name]
  - Isehara Clinical trial center, Zenba-acupuncture and moxibustion clinic; [name]
  - Kenkou Data House Inc.; [name]

**13-2.** **Methods of retaining and disposing of samples and information**

Paper information about the research will be stored in a locked archive at the Center for Clinical research. Electronic data will be stored on a hard disk managed by the principal investigator at the Center for Clinical research. At the end of the research, the electronic data will be stored on CD-R or DVD in a locked archive at the Center for Clinical research, together with the paper-based information about the research. Information about the research will be destroyed after a specified period (10 years from the date of the final publication of the results of the research).

**13-3.** **Handling of research results related to research subjects**

1. if the individual subject of the research wishes the information to be disclosed, the results will be disclosed.
2. If the research subject does not wish the information to be disclosed, the results will not be disclosed.
3. If a person other than the research subject wishes the information to be disclosed, the results will not be disclosed in principle.

**14.** **The payment of money and compensation for the conduct of the clinical trial**

**14-1.** **Payment of monies related to the conduct of the clinical trial**

The honorarium to the research subjects for participating in this study will be 2000 yen worth of electronic money.

**14-2. Insurance and Compensation**

This clinical trial is covered by clinical trial insurance. If health damage occurs to research subjects as a result of the implementation of the research, the principal investigators and sub-investigators will provide adequate medical treatment and other appropriate measures and will endeavor to investigate the cause of the damage. Medical expenses for such treatment will be covered by health insurance, and the research subjects will pay for any out-of-pocket expenses.

In addition, compensation will be paid by the clinical trial insurance for death or disability of classes 1 to 14 under the Adverse Effects Relief System for Drugs.

**15.** **The publication of information on clinical trial**

Before starting a study, the details of the research plan shall be recorded in the jRCT (Japan Registry of Clinical Trials), a database maintained by the Ministry of Health, Labour and Welfare (MHLW), and made public.

